**Fig. 1 Fig1:**
[figure not shown]
Participant recruitment and flow through the study

Table 1 gives an overview of the assessment/measures. PST and MI participants will be assessed at pre-intervention (time 1), post-intervention (time 2), and at 2 months follow-up (time 3). WC participants will be assessed at time 1 and 2, and will then be randomly assigned to the PST or MI intervention. Participants will complete a series of questionnaires at all assessment time points. Participants names will be coded in the data file for anonymization and the code key will be stored in a different file. Since it is not possible to mask condition assignment for the participants or the experimenter, we will assess and control for outcome expectations regarding the assigned intervention in order to control for potential effects on outcomes (see recommendations by Boot et al. [10]).

**Table 1 Tab1:** Instruments assessing inclusion and exclusion criteria, primary/secondary outcomes, moderators, mediators, and common factor

Concept	Measurement (items)^a^	Time points^b^			
		T0	T1	T2	T3
Inclusion/exclusion criteria					
Clinical level of psychopathology	BSI-18 (18)	x			
Experience with PST/MI	-	x			
Primary outcome measure					
Functional athletic behavior	Ambulatory assessment		x	x	x
Secondary outcome measures					
Psychological variables					
State anxiety	CAI-S (scales cognitive and somatic anxiety, 8)		x	x	x
Cognitive interference	TOQS (17)		x	x	x
Negative outcome expectation	CAI-S (confidence scale inversed, 4)		x	x	x
Athletic performance					
Objective measures	E.g., win/lose, points scored		x	x	x
Subjective measures	Self-rated measures of performance		x	x	x
Mediators					
Use of psychological skills	TOPS (scales self-talk, imagery, goal-setting, relaxation and activation, 20)		x	x	x
Ability to control thoughts and emotions	TOPS (scales negative cognitions and emotional control, 8)		x	x	x
Mindfulness	FFMQ-SF (24) & AMQ (16)		x	x	x
Acceptance of (unpleasant) experiences	SEC-27 (acceptance scale, 3) & AAQ-II (inversed, 9)		x	x	x
Defusion	EQ (decentering scale, 7), DSS (12)		x	x	x
General attention	ANT		x	x	x
Moderators					
Task difficulty	-		x	x	x
Importance of game/competition	-		x	x	x
Demographic characteristics	-	x			
Task- & ego-orientation	TEOSQ (13)		x		
Self-esteem	RSC (10)		x		
Self-compassion	SCS short form (12)		x		
Common factor & practice time					
Athletes’ expectancy of the intervention	- (3)		x		
Practice time	Practice sheets			x	x

^a^
*BSI* brief symptom inventory, *CAI-S* competition anxiety inventory state, *TOQS* thought occurrence questionnaire sport, *TOPS* test of performance strategies, *FFMQ-SF* five facets mindfulness questionnaire short form, *AMQ* athletic mindfulness questionnaire, *SEC-27* self-assessment of emotional competencies, *AAQ-II* acceptance and action questionnaire, *EQ* experience questionnaire, *DSS* decentering scale for sport, *ANT* attention network test, *TEOSQ* task ego orientation sport questionnaire, *RSC* rosenbergs’s self-esteem scale, *SCS* self compassion scale

^b^T0 = Before randomization T1 = pre-intervention, T2 = post intervention, T3 = 2 months follow up

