### Study design and group allocation

Figure 1 shows an overview of the procedure (parallel group design). After a first contact and checking for inclusion and exclusion criteria (time 0), athletes will be stratified for gender, sport, and performance level, then randomly assigned to either the PST group, the MI group, or the WC group, and will be informed about their experimental condition. Members of the same team (i.e., curling, volleyball, or hockey) will be assigned to the same intervention group. For randomization, a computer-generated random-number sequence will be prepared in advance and sealed in opaque, consecutively numbered envelopes by an independent researcher. An independent researcher will open the envelopes in sequence based on client number, to determine the participant’s assignment to the groups.

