#### Inclusion criteria and common factor

We will use the short version of the Brief Symptom Inventory (BSI-18) [68] to assess clinical level of psychopathology. A total scale score of the BSI (*Global Symptom Index*, GSI) of T > 60 indicates a significant level of psychopathology. In psychotherapy, treatment expectancies have been shown to predict change in outcome variables (e.g., depression, [29, 55]). For that reason we will examine the associations between athletes’ expectancies (after the randomization) and subsequent changes in the primary and secondary outcome variables.

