### Statistical analysis

All analyses will be conducted as intent-to-treat. To assess if randomization is successful in balancing demographic characteristics across the treatment groups, we will compare age, use of psychological skills, mindfulness, and performance level using Student’s t-tests. Two-way (group x time) repeated measures ANOVAs will be used to answer the question regarding whether the intervention (independent variable) had an effect on the primary and secondary outcome measures (dependent variables). Significant overall effects will be followed up with post hoc tests and contrasts between intervention programs (e.g., PST and MI together compared to the WC group). Significance levels will be set at *p* = .05. If there are significant differences between different intervention sub-groups, we will perform multilevel analyses. To test the mediation and moderation models, we will follow the requirements for mediation and moderation suggested by Hayes [36]. The first three authors of this manuscript will have access to the full dataset.

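### The protocol says it will control for expectancy measured after athletes know their arm; applied to the waiting-list contrasts, this would no longer estimate the randomised effect, and the statistical section names no such covariate

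*Protocol article*

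**What the plan says.** Three sections of the protocol article bear on this.

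- **Study design and group allocation.** Athletes are stratified, "then randomly assigned to either the PST group, the MI group, or the WC group, and will be informed about their experimental condition". Since neither athletes nor experimenter can be masked, "we will assess and control for outcome expectations regarding the assigned intervention in order to control for potential effects on outcomes". For the control arm, "WC participants will be assessed at time 1 and 2, and will then be randomly assigned to the PST or MI intervention".
- **Inclusion criteria and common factor.** Expectancy is justified by the remark that in psychotherapy "treatment expectancies have been shown to predict change in outcome variables". The use described is an association between athletes' "expectancies (after the randomization) and subsequent changes in the primary and secondary outcome variables". Table 1 lists three expectancy items, marked at T1 only; its footnote reads "T0 = Before randomization T1 = pre-intervention".
- **Statistical analysis.** "All analyses will be conducted as intent-to-treat". Primary and secondary outcomes are tested with a group-by-time repeated measures ANOVA. No covariate is named.

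**The concern.** Adjusting for a variable measured before allocation leaves the randomised comparison intact. Expectancy here is measured after athletes learn their arm, and it is about that arm, so it can be a consequence of allocation. The article's own rationale is that expectancy predicts change in outcome. On that reasoning it can lie on the path from allocation to FAB.

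Conditioning on it in an active-versus-WC contrast would replace the total effect of being offered PST or MI with a direct effect at fixed expectancy. That direct effect is interpretable only if nothing unmeasured drives both expectancy and self-rated FAB, which randomisation does not secure. Nor would it repair the lack of masking.

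The covariate also has no comparable meaning in WC, because at T1 these athletes have no assigned intervention to hold expectations about. The contrast affected is the one in the primary hypothesis, each active arm against waiting list.

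**Working it through.** **1. Timing.** The order is: randomisation, disclosure of the arm, expectancy at T1, intervention, outcome at T2, and only then PST or MI for WC athletes. Expectancy is therefore a post-allocation variable, and its referent is absent in WC over the T1 to T2 comparison.

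**2. The sections side by side.** Study design and group allocation commits to controlling for expectancy. Statistical analysis specifies a model without it. Inclusion criteria and common factor describes only associations with change. A reader cannot tell from these whether the reported effect is adjusted.

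**3. The planned effect as a benchmark.** Inputs from Participants and power analysis: d = 0.6, one-sided α = 0.05, power 80%. The normal formula gives n = 2(1.645 + 0.842)²/0.6² = 34.4, so 35 per group. The t-test version gives 35.04, rounded up to 36 per group and 108 in total, as stated. Power at 36 per group is 0.81 (t) to 0.82 (normal). The sample size is not in dispute.

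**4. What adjustment would do.** Let D be the active-minus-WC difference in expectancy in within-arm SDs, and b the within-arm slope of FAB on expectancy, in SD per SD. Neither is in the document; both are assumptions. For two equal arms:

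- adjusted effect = 0.6 − b × D
- variance multiplier for the arm coefficient = (1 + D²/4) × (1 − b²), collinearity times the residual variance left unexplained
- SE = √(2/36) × √(multiplier)
- power = Φ(adjusted effect/SE − 1.645)

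| D | b | Shift | Adjusted effect | Share of 0.6 removed | Variance multiplier | Power |
|---|---|---|---|---|---|---|
| 0 | 0.1 to 0.3 | 0 | 0.60 | 0% | 0.99 to 0.91 | 0.82 to 0.85 |
| 0.5 | 0.1 | 0.05 | 0.55 | 8% | 1.0625 × 0.99 = 1.05 | 0.74 |
| 1 | 0.2 | 0.20 | 0.40 | 33% | 1.25 × 0.96 = 1.20 | 0.46 |
| 1 | 0.3 | 0.30 | 0.30 | 50% | 1.25 × 0.91 = 1.14 | 0.33 |
| 1.5 | 0.2 | 0.30 | 0.30 | 50% | 1.5625 × 0.96 = 1.50 | 0.27 |
| 1.5 | 0.3 | 0.45 | 0.15 | 75% | 1.5625 × 0.91 = 1.42 | 0.13 |

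**5. Simulation check.** A linear model with 400,000 simulated athletes, D = 1 and b = 0.2, gave 0.60 unadjusted and 0.40 adjusted. A second case gave expectancy no effect on outcome but let one unmeasured cause load 0.4 on each. The within-arm slope is then 0.4 × 0.4 = 0.16, and the estimate fell from 0.59 unadjusted to 0.43 adjusted. A shared cause is enough to bias the adjusted contrast without any true mediation.

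**The case against.** The strongest reply is that no adjusted PST-WC or MI-WC model is actually specified. The phrase about controlling for expectations is one clause in a paragraph on masking; it names no model, contrast or outcome, and defers to cited recommendations that are not at hand. The only statistical section gives an ANOVA without it. This stands. A reader might infer that the trial's main result will be an expectancy-adjusted effect, and the document does not support that.

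Second, expectations about an assigned intervention may be meant only for athletes assigned to PST or MI, where the question is comparable. The document does not say whether or how WC athletes answer. A reader might therefore infer that WC values will be missing and the control arm lost, or that they will be low enough to make expectancy nearly a proxy for arm. Both are conjecture. The collinearity factors of 1.25 to 1.56 at D = 1 to 1.5 are mild and do not describe a near-proxy.

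Third, the intent-to-treat statement settles nothing. It concerns analysing athletes as allocated and neither requires nor forbids a covariate. It would be breached only if missing WC values removed athletes from an adjusted model.

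What does not stand is the plea that a condensed article leaves covariates to the analysis plan. Controlling for expectancy is a rule that the article states, not a detail that it omits. Examining expectancy in an unmasked trial with a self-rated outcome is a legitimate aim, but covariate adjustment against WC does not achieve it.

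**Conclusion.** The point holds in conditional form. The article states an adjustment for a variable measured after disclosure of the arm, with no comparable meaning in WC, and its statistical section does not carry that adjustment. The sections must be reconciled. If the stated rule were followed in PST-WC or MI-WC, the estimate would not be the total randomised effect and would be open to confounding between expectancy and FAB.

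The size cannot be derived from the document. It runs from nothing, if expectancy does not differ by arm and shares no cause with FAB, through 8% of the planned effect at the small assumed values, to 33 to 50% at D = 1 and slopes of 0.2 to 0.3, where the variance also rises by about 14 to 20%. At D = 1.5 with the same slopes, the variance rise is about 42 to 50%. These figures are illustrations, not predictions. The change in what is being estimated is the main problem, and it does not rest on any one of them.

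**What to change.** Amend the sentence in Study design and group allocation to say that the primary and secondary PST-WC and MI-WC estimates are not adjusted for expectancy, which agrees with the ANOVA in Statistical analysis. State the two uses that remain:

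- expectancy as an exploratory predictor of change within PST and within MI, in line with Inclusion criteria and common factor;
- a labelled sensitivity analysis adjusting for expectancy in PST versus MI only, where the question has a similar referent in both arms.

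The cost is a sentence or two of text. No data collection changes, no athlete is added, and the planned expectancy analyses are kept.

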### Description of the PST and MI intervention

The PST intervention will be adapted from PST programs like Ebersbächer’s *Mental Training* [15]. It involves the practice of four psychological skills (self-talk, imagery, goal-setting, and arousal control) and will be based on the latest guidelines and recommendations about instruction and application of these skills [1, 27, 73, 77]. A sport psychologist trained in specialized PST interventions will explain the expected sport-specific benefits to the participating athletes and advise athletes to do homework between group sessions.

The MI will be adapted from mindfulness-intervention programs, including Mindfulness-Acceptance-Commitment (MAC) [25], Acceptance and Commitment Therapy (ACT) [38], and Mindfulness-Based Stress Reduction (MBSR) [45]. A sport psychologist trained in specialized mindfulness-based interventions will explain the expected sport-specific benefits to the participating athletes and advise athletes to do formal and informal mindfulness practices at home between group sessions.

The interventions will be realized in groups of six athletes each, leading to six sub-groups in each condition (6 × 6 = 36 athletes, see power analysis). A manual will accompany the instructions for the interventions. All components of both interventions must be administered according to the manual’s specifications. Two independent raters will evaluate the adherence to each intervention on the basis of video recordings. In addition to psycho-education and practice at home guided by audio files that can be played on computers or portable devices such as smart phones. All participants will also be provided with a calendar of their exercises to tick off as they are completed, and daily text messages will remind them to practice their PST or mindfulness exercises. Each intervention consists of four 2-h sessions over the course of 5 weeks. Participants will be advised to practice daily and record their amount of practice. All sessions will conducted at the center for elite sports of the Swiss Federal Institute of Sport.

### Measures

#### Primary outcome measure

We will assess FAB as the primary outcome measure using an *ambulatory assessment*^1^ procedure, that samples subjective psychological variables in real time and the natural environment [72]. We will analyze three to four in-game/match sequences (S1 to S3 or S4, respectively) specific for each sport. In curling we will evaluate the first end (S1), the end before half-time (S2), the first end after half-time (S3), and the last end of the game (S4).^2^ In volleyball we will analyze the second and third set of one game^3^ by evaluating the first 5 points in each set (S1 and S3) and the last 5 points in each set (S2 and S4). In tennis we will analyze the first two sets of one match: the second and the third game^4^ (S1 and S3) and the last two games of the set or the tiebreak (S2 and S4). In hockey we will analyze each period (S1-S3) of one game.^5^

After each sequence we will evaluate whether athletes behaved functionally in the last sequence. We will ask the athletes themselves to rate the last end (curling), the last 5 points (volleyball), the last two games or the tiebreak (tennis), or the last period (hockey). It is common practice in other studies using ambulatory assessment to use only a few items to keep the interference of the measurement to a minimum (e.g., [75]). To assess FAB, athletes will rate the following questions from 0 (*no agreement*) to 100 (*total agreement*) on a tablet computer using a scroll bar:Rate regardless of the result or outcome: In the *last sequence*, my movements and actions were of a high quality (precise, energetic, well timed, etc.).Rate regardless of the result or outcome: In the *last sequence*, I was focused on the task.Rate regardless of the result or outcome: In the *last sequence*, I behaved on the pitch/field/ice as the athlete that I would like to be.

Before the first assessment, athletes will be given instructions in training when and how to answer the questions and then answer the questions in an actual game/competition for familiarization.

#### Secondary outcome measures

Secondary outcomes are *negative outcome expectancies* (assessed directly before the game or match) as well as *somatic* and *cognitive competition anxiety* (directly after the game or match), which are all measured by the respective scales of the Competition Anxiety Inventory State (CAI-S) [11]. *Cognitive interference* (directly after the game or match) is measured by the Thought Occurrence Questionnaire for Sport (TOQS) [61]. In addition, we will assess objective (win/lose, performance indicators relevant for the sports discipline, such as shot percentages, points scored, winners/unforced errors, and goals/assists) and subjective (self-rated) measures of performance.

#### Mediators

We will use all these measurements in all three study groups to examine whether changes are specific for the expected groups. *Use of psychological skills* (manipulation check for PST) will be assessed by the subscales *self-talk*, *imagery*, *goal-setting*, *activation* and *relaxation* of the Test of Performance Strategies (TOPS) [65]. Being able to control emotions and thoughts will be measured by the TOPS subscales *emotional control* and *negative cognitions*.

We will use short form of the Five Facet Mindfulness Questionnaire (FFMQ-SF) [8] and the Athletic Mindfulness Questionnaire (AMQ), [80] to assess *mindfulness* (manipulation check for MI); the respective subscale of the Self-Assessment of Emotional Competencies (SEC-27) [4] and the Acceptance and Action Questionnaire II (AAQ-II) [9] to assess *acceptance*; and the *decentering* subscale of the Experience Questionnaire (EQ) [20] and the Decentering Scale for Sport (DSS) [79] to assess *defusion*.

The Attention Network Test (ANT) [17] will be used to assess *general attention* (i.e., *orienting*, *conflict monitoring*, and *alerting*). To assess perceived *attention control in games or competitions*, we will use the respective subscale of the TOPS.

#### Moderators

We will assess *task difficulty* by having participants rate their opponents’ performance after each sequence from 0 (*very bad*) to 100 (*very good*), by assessing the opponents’ ranking/seeding (lower, equal, higher), and the ongoing score. To assess the *importance of the game/match*, we will have the athletes rate the importance on a scale from 1 (*not important*) to 7 (*very important*) before the game or the match. In addition to basic demographic factors (i.e., age, gender, type of sport, performance level, and experience with PST and MI), we will assess *task and ego orientation* using the Task and Ego Orientation in Sport Questionnaire (TEOSQ) [59]; *self-esteem* using Rosenberg’s Self-esteem Scale (RSC) [13]; and *self-compassion* using the short form of the Self-Compassion Scale (SCS) [41, 58].

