### Moderators

To our knowledge no studies have examined factors potentially moderating the effectiveness of PST or MI. Such information is of crucial importance as it may specify the influence of certain situational variables or identify groups of individuals likely to either benefit from an intervention or not. In order to examine for whom and under which conditions PST and MI are (not) effective, three types of moderators are investigated in the present study. Most importantly, we will look at *situational variables*, i.e., task difficulty and the importance of the game or competition for the individual athlete. The other two kinds of moderators can be divided into *basic demographic factors* (e.g., age, gender, kind of sport, performance level, and previous experience with PST and MI), and *individual characteristics* that research has identified as being relevant in situations of athletic performance like task- and ego-orientation [16], self-esteem [50], or self-compassion [3, 19, 54].

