### Study objectives and hypotheses

The primary objective of this study is to assess the effects of PST and MI in promoting FAB in elite athletes. We hypothesize that both active interventions are more effective than a waiting-list control condition in promoting FAB. We do not expect PST to be superior over MI or vice versa; rather, they are expected to increase FAB through different routes.

Thus, the secondary objective is to examine potential factors that mediate the effects of PST and MI. We assume that the effect of PST on FAB is mediated by the use of psychological skills (the manipulation check of the PST intervention) and the experienced ability to control one’s thoughts and emotions. We expect the effect of MI on FAB to be mediated by participants’ self-rated mindfulness (the manipulation check of the MI intervention) and acceptance of/defusion from unpleasant experiences. Finally, we hypothesize the effects of both PST and MI on FAB to be mediated by general level of attention and perceived attention control in games or competitions.

A third objective is to examine potential moderators of the effects of PST and MI. We assume that the more athletes interpret their current experience as something that has to be regulated, the more they profit from regulation or coping strategies being utilized/taught in PST and MI. We therefore hypothesize that athletes high in ego orientation or those with low values of self-esteem and self-compassion benefit the most from PST and MI. Such athletes might perceive performance situations as threatening for their psychological needs to a greater chance [24, 28], especially when the athletic task at hand is difficult or the competition is perceived as important. Perceived threat might lead to, for example, more competition anxiety, negative outcome expectations, or cognitive interference. In addition, we aim to investigate the role of treatment expectancies (common factor) and treatment adherence for improvements in FAB.

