## Method

### Participants and power analysis

The target group are elite, sub-elite, and recreational athletes from four sports (curling, volleyball, i.e., indoor and beach, tennis, and hockey, i.e., floorball and ice hockey). We chose these sports because they are suited to sample comparable short sequences (see primary outcome below) within a game or a competition, as opposed to, for example, soccer. Athletes who are members of the respective Swiss national sport associations will be contacted and offered the opportunity to participate. Criteria for exclusion are a likely mental disorder, significant previous experience with PST or MI, less than 4 h of athletic training per week, or being younger than 18.

The sample size calculation is based on differences between the waiting-list control group (WC) and one of the treatment groups (PST or MI) after the intervention. Based on previous research, we assume medium effect sizes of d = .6 [39]. Testing one-sided, given that α = .05 and a power of 80 %, we would need 108 participants (36 for each group) to be able to detect the effect.

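### Task difficulty is measured partly by the ongoing score and the athlete's own rating of the opponent; at T2 and T3 both follow treatment and can depend on FAB, so a moderation test using them is biased

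*Protocol article*

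**What the plan says.** The Moderators section under Current study introduces situational variables as the most important of three types of moderator. It names two: "task difficulty and the importance of the game or competition for the individual athlete".

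The Moderators section under Measures gives task difficulty three measures: a 0 to 100 rating of the opponent, made by the athlete after each sequence, and the opponent's "ranking/seeding (lower, equal, higher), and the ongoing score". Table 1 schedules task difficulty at T1, T2 and T3.

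The third objective, under Study objectives and hypotheses, expects athletes high in ego orientation or low in self-esteem or self-compassion to benefit most. They are thought more likely to feel threatened, "especially when the athletic task at hand is difficult or the competition is perceived as important".

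Four other statements bear on this:

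- **Background:** FAB is a necessary, though not sufficient, condition of optimal performance.
- **Primary outcome measure:** athletes rate their own FAB after each of three or four sequences.
- **Secondary outcome measures:** the match result and points scored are outcomes.
- **Study design and group allocation:** participants cannot be masked.

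Statistical analysis refers the moderation models to a cited methods source and does not separate the three difficulty measures.

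**The concern.** A moderator of a treatment effect should not itself be changed by treatment or by the outcome. Two of the three difficulty measures do not meet this condition at T2 and T3.

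- **Ongoing score.** On the protocol's own theory, an intervention that raises FAB should improve performance and so the score. The running form of a secondary outcome then also serves as a moderator.
- **Opponent rating.** The same unmasked athlete gives it after the same sequence as the FAB rating. An athlete who is playing well may judge the opponent weaker.

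At stake is the question of under what conditions the interventions work, which the Abstract and Discussion present as an aim. With a variable that treatment shifts, a given level of measured difficulty means different true difficulty in the two arms.

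The other moderators are safer. Importance is rated before the match, and ego orientation, self-esteem and self-compassion are taken at T1 only.

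**Working it through.** **1. The plan's own figure.** Sample size is the only figure with a calculation behind it, and it concerns the main effect ("we assume medium effect sizes of d = .6", one-sided α = .05, power 80%). The normal formula gives 2(1.645 + 0.842)²/0.6² = 34.4, so 35 per group. The t-test needs 35.04, so 36 per group and 3 × 36 = 108, as stated; power at 36 per group is 0.81. It is reproduced and not in dispute. No figure is given for moderation.

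**2. Timing of each measure at T2 and T3**

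| Measure | When it arises | Can FAB in that match move it? |
|---|---|---|
| Ranking/seeding | before the match | no |
| Ongoing score | during the match | yes |
| Opponent rating | after each sequence, with FAB | yes |

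**3. Illustrative model.** All inputs except 36 per arm and d = 0.6 are assumptions.

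- One active arm against waiting list, A = 1 or 0.
- True difficulty D ~ N(0, 1), balanced between arms.
- Y (FAB) = 0.6A − 0.3D + c·A·D + ε, with SD(ε) = 1.
- Measured difficulty M = D − a·Y + 0.5e, with e ~ N(0, 1).
- Y is regressed on A, standardised M and their product; 1,500 runs per setting; two-sided 5% test.

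Here a is the strength with which measured difficulty falls as FAB rises.

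**4. Hand check at a = 0.5, c = 0.**

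- M = 1.15D − 0.3A − 0.5ε + 0.5e.
- Within-arm Var(M) = 1.3225 + 0.25 + 0.25 = 1.8225.
- Including the arm difference, the variance is 1.845 and the SD 1.36.
- Shift in M between arms: −0.3/1.36 = −0.22 SD, although true difficulty is balanced.
- Within-arm slope of Y on M: (−0.3 × 1.15 − 0.5)/1.8225 = −0.464.
- Treatment effect at mean M: 0.6 − (−0.464)(−0.3) = 0.46. The simulation gives 0.46.

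**5. Simulation, equal residual SDs**

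| a | Shift in M (SD), c = 0 | Effect at mean M, c = 0 | Interaction per SD of M, c = 0.4 | Interaction lost | Power for interaction |
|---|---|---|---|---|---|
| 0 | about 0 | 0.61 | 0.358 | – | 30% |
| 0.25 | −0.12 | 0.54 | 0.307 | 14% | 26% |
| 0.5 | −0.21 | 0.46 | 0.221 | 38% | 17% |
| 1 | −0.35 | 0.31 | 0.052 | 85% | 6% |

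The loss is taken against the a = 0 row, for example 1 − 0.221/0.358 = 38%. That row is already below 0.4 through measurement noise alone: 0.4/√1.25 = 0.358. With c = 0 the rejection rate stays near 5%.

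**6. Unequal residual SDs.** The within-arm slope contains a term −a·Var(ε)/Var(M), so arms with different Var(ε) have different slopes even without moderation. With the treated arm's residual SD 30% lower and c = 0, rejection is 5%, 7%, 14% and 25% for a = 0, 0.25, 0.5 and 1. The spurious interaction at the last three is +0.10, +0.15 and +0.19, which has the sign of greater benefit under difficulty. With c = 0.4 the estimate goes from 0.35 to 0.42, 0.43 and 0.33, so attenuation is not assured.

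**7. Sensitivity.** Varying the measurement noise and the direct effect of difficulty on FAB, a = .3 costs about 8–20% of the interaction and a = .7 about 40–80%. If M instead uses the score at sequence start, driven by the previous sequence's FAB, a true interaction of .30 is estimated as .23 at a = .3 and .15–.16 at a = .7. An equally noisy exogenous measure gives .24–.25. The loss at .7 is then about a third to two fifths (1 − .16/.24 = 33%; 1 − .15/.25 = 40%).

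**The case against.** **The text lists measures, not an analysis.** The protocol does not say that the three are pooled, weighted equally or each crossed with treatment. A reader might infer a single contaminated index, and the text does not support that. What stands is narrower: all three are declared measures of the moderator, all are scheduled after treatment, and nothing separates the one fixed before the match from the other two.

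**The ongoing score may mean the score when a sequence begins.** It would then precede that sequence's FAB. This reading is fair and softens the bias. The score at T2 still follows treatment and earlier FAB in the same match, so the bias does not vanish.

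**Athletes are told to rate FAB regardless of the result.** This may weaken the path from score to rating. It does not touch the path from FAB to score.

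**Low power is mainly a matter of sample size.** This is correct: under these assumptions even an uncontaminated moderator has 30% power, and mild dependence (a = 0.25) only lowers it to 26%. The case for change rests on bias more than on lost power.

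**Difficulty is not the core of the third objective.** Its explicit hypotheses concern traits measured at T1, and difficulty shares first place among moderators with importance. This limits the weight of the point without removing it.

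**Conclusion.** The point holds as a flaw in a stated but third-ranked objective. Two of the three difficulty measures are post-treatment at T2 and T3 and can depend on FAB, so a treatment-by-difficulty test using them is biased. The usual direction is attenuation of both the conditional treatment effect and the interaction.

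The size rests wholly on assumed dependence: about 10% to 80% of the interaction for dependence of .3 to .7, less with the score at sequence start.

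Three stronger readings are not supported:

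- **That around half or more of the interaction is lost even at weak dependence.** At .3 the loss due to FAB is about 8–20%; the rest of any shortfall is ordinary measurement noise.
- **That the harm can only be missed moderation.** This needs equal residual variances. With the treated arm's SD 30% lower, false positives reach 7% to 25%.
- **That the trial's main conclusion is at risk.** The primary group-by-time analysis and the sample size do not use task difficulty. The T1 values precede the intervention.

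**What to change.** In the Moderators section under Measures, state that the opponent's pre-match ranking/seeding relative to the athlete is the task-difficulty moderator of record for the treatment effect. Add that the ongoing score, taken at the start of each sequence, and the athlete's rating of the opponent enter only exploratory analyses labelled as post-treatment.

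This takes one or two sentences, and ranking/seeding is already collected. The price is a coarser moderator with three levels that does not vary within a match and so cannot describe changing difficulty during play. The exploratory analyses keep that information available, with its limits stated.
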